#### Co-Researchers

After expressing their interest in collaborating with the TobExA team, prospective co-researchers will participate in a preliminary onboarding interview (approximately 1 hour) to assess their personal and professional development goals, research interests, current skills and strengths, and availability. Those who are able to commit approximately 5 to 10 hours per week for 3 months (with flexibility as needed) and whose interests are aligned with the study or research generally will be invited to join the study as co-researchers. Before being assigned research tasks, co-researchers will participate in a group training on human research protections and receive an in-depth introduction to the TobExA study. Co-researchers will then be assigned weekly tasks based on study needs and their individual interests and goals. They may also begin to attend TobExA study team meetings at this time.

Co-researchers will participate in 30-minute biweekly individual check-in meetings with the youth engagement liaisons to discuss tasks and troubleshoot any issues or concerns. Every 2 weeks, all co-researchers will participate in a 1.5-hour group meeting led by the youth engagement liaisons where co-researchers will share updates on their tasks; build community with fellow co-researchers and youth engagement liaisons; and collaborate on research tasks, such as analyzing interview data to inform the TobExA intervention (with guidance from the youth engagement liaisons). Co-researchers may complete most of their assigned tasks remotely (with many tasks designed to be completed on a smartphone if a computer is not easily accessible), with group meetings predominantly held in person. They will have access to workspaces with computers and internet at the community and academic partners’ offices.

We acknowledge that substantial attrition among co-researchers may occur during the expected 3-month engagement period, partly due to their developmental and life stage (characterized by educational, familial, and personal transitions and changes) and the many stressors and competing priorities for youth with current or previous experiences of homelessness or housing instability [76-78]. To support the retention of co-researchers, we will monitor attendance at weekly group and individual meetings. If waning engagement is noted, youth engagement liaisons will work collaboratively with youth and community partners to assess the individual needs of co-researchers and determine the most appropriate support strategies. These may include additional development opportunities or, if necessary, a compassionate offboarding process. Exit interviews and periodic focus group discussions (detailed subsequently) will provide additional insights into reasons for disengagement and co-researcher retention strategies and will be used to drive changes to strategies as needed. This structured process, along with the co-researcher role’s co-designed nature between youth, academic, and community partners, is anticipated to promote engagement in the long term. Several of the authors have experience collaborating with youth in other youth participatory action research studies in which study goals were achieved with as few as 2 to 4 highly involved youth collaborators [79,80]. Thus, even if we experience high rates of attrition among co-researchers, we expect to engage a sufficient number of youth collaborators throughout the study period to meet our goals.

#### Advisors

As noted earlier, advisors will participate in specific opportunities to provide feedback on the TobExA intervention. These opportunities will be synchronous, such as group or individual meetings with study staff (in person or over Zoom), or asynchronous, such as providing feedback via email or a secure messaging app. Synchronous opportunities (eg, group meetings) will be coled by co-researchers who will develop the agenda, cofacilitate discussions, and take the meeting minutes. Advisors may participate in 1 or more feedback opportunities (we expect to hold a minimum of 2 feedback opportunities during the study period) and will receive US $19 per hour for their participation, with additional stipends to cover transportation and childcare as needed. Advisors will be given (in person) or mailed a check after participating in a feedback opportunity.

#### Youth Engagement by Research Stage

Multimedia Appendix 1 provides a visual representation of the TobExA intervention research process (including the 6 steps of IM [64]), crosswalked with youth collaborator participation time points and activities. The first phase of IM (step 1) is the *needs and assets assessment*, which involves developing a *logic model of the problem*. During this phase, we will conduct formative interviews with stakeholders and youth to assess reasons for tobacco and cannabis use among youth experiencing homelessness as well as needs to prevent and reduce use in this population (ie, needs-assessment phase). We will also focus on assessing the context in which the intervention will be implemented to identify strategies to support intervention fit and sustainability. Although co-researchers will not be involved in data collection for this initial phase of the research process, they will provide feedback on and contribute to the development of the *logic model of the problem* during group meetings led by the youth engagement liaisons. These early contributions will be essential to ground the IM process in the local context as informed by the lived experiences and community knowledge of co-researchers and other stakeholders who are familiar with the local context (through lived experience, work roles, etc).

Co-researcher and advisor engagement will be especially critical during the subsequent stages of the research process, including development of the intervention (IM steps 2-4), planning for implementation and evaluation (IM steps 5-6), and piloting the intervention. Throughout these stages, co-researchers and advisors will provide synchronous and asynchronous input that will be directly incorporated into the intervention research process. Specifically, co-researchers will participate in several structured activities to ensure their equitable contributions to the intervention development process. This includes participating in analysis of qualitative data gathered during IM step 1, reviewing and providing feedback on materials to consider for inclusion in the intervention (eg, existing tobacco intervention materials and resources), and attending intervention development meetings with the full TobExA team. Co-researchers will also be invited to lead presentations for the TobExA team to share their ideas and recommendations for the intervention. Co-researchers will be involved in piloting the intervention (eg, supporting recruitment, data collection, and cofacilitation) and supporting dissemination of findings (eg, via scientific conferences, community-based presentations and events, and fact sheets).

Co-researchers will lead discussion sessions or asynchronous communication with advisors to gather their feedback during 2 key phases of the IM process (steps 3-4 and 5-6). Advisors will be asked to respond to specific open-ended prompts or discussion questions that will shape decisions regarding the intervention content and implementation strategies. For example, we may gather feedback from advisors to identify the best approach to hosting intervention group sessions based on age, with questions such as, “The intervention will include group sessions. If you were attending a group about reducing tobacco and/or cannabis use, what age range would you feel most comfortable with? Why?” Advisors will also be invited to provide feedback on recruitment strategies and other related considerations for piloting the intervention, such as appropriate incentives for participation, strategies for data collection, and strategies for gathering detailed participant feedback. Co-researchers will summarize and share feedback from the advisors with the full TobExA team to ensure advisors’ contributions are meaningfully integrated into the intervention research process (at TobExA team meetings or via asynchronous communication). Although we do not currently have plans to engage advisors in findings dissemination, we may schedule feedback opportunities as part of findings dissemination to “member check” our interpretations and gather recommendations for next steps in the TobExA intervention research process (eg, how to improve the intervention for a future efficacy trial).

### Measures and Tracking

#### Overview

Multiple strategies will be implemented to evaluate and document youth engagement strategies and processes throughout the study. To document the process of engagement and identify opportunities for quality improvement, youth engagement liaisons and other TobExA team members working directly with youth collaborators will write field notes and ethnographic memos based on their experiences and learnings (yielding qualitative data).

We will collect data from youth collaborators to document sociodemographic characteristics of youth engaged (co-researchers and advisors—age, education, race, ethnicity, sex assigned at birth, gender identity, transgender status, sexual orientation, and recent housing experiences), evaluate the impact of collaboration on the personal and professional development of youth (co-researchers only), and identify opportunities for quality improvement in our engagement processes (co-researcher and advisors).

Co-researchers will complete surveys at multiple time points, participate in periodic focus group discussions, and complete a semistructured exit interview (approximately 45 min long) when they officially end their time as a co-researcher. Survey measures were pilot-tested with a subsample of co-researchers via “think-aloud” cognitive interviews (mean 105, SD 15 min), which allow youth to verbally discuss the survey questions and explain the factors contributing to their answers [81]. Advisors will complete short surveys after participating in a feedback opportunity. Surveys were piloted with members of the community partner YAB. Figure 1 presents a visual overview of evaluation methods. We further detail these evaluation strategies in the subsequent sections.

**Figure 1 figure1:**
[figure not shown]
Youth engagement evaluation methods.

#### Field Notes and Ethnographic Memos

Youth engagement liaisons and other TobExA team members working directly with youth collaborators will write semistructured field notes after each biweekly meeting with the co-researchers and advisors and weekly unstructured ethnographic memos on the overall youth engagement and collaboration process [82]. Field notes will include prompts to narratively describe the following: (1) barriers to and facilitators of equitable and sustainable youth engagement and collaboration, (2) the application of key youth participatory action research and community-based participatory research principles to our youth engagement processes, and (3) how youth engagement and collaboration activities are connected to and facilitating the completion of TobExA study aims. Field notes will also capture noteworthy milestones and activities in co-researcher development, such as participation in major training and professional development opportunities.

Ethnographic memos will be in the form of unstructured narrative reflections regarding co-researcher–related activities and progress. Memos will document key challenges or needs in the youth engagement process and identify opportunities to refine youth engagement and collaboration strategies. Memos will be regularly reviewed by the academic co–principal investigator and other supporting coinvestigators, allowing for real-time or near real-time communication regarding emergent challenges to be addressed (ethical, logistical, and process related).

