#### Youth Co-Researcher Semistructured Exit Interviews

To document co-researchers’ experiences and solicit feedback on our engagement processes, semistructured exit interviews will be conducted with co-researchers when they offboard from their role. Key constructs of interest include general experiences as a co-researcher, perceptions of personal and professional development over time, contributions to the study, team dynamics and communication, key challenges, and opportunities for improvements to youth engagement processes.

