### Planned Analysis

Qualitative data (field notes, ethnographic memos, and semistructured exit interviews) will be analyzed using applied thematic analysis procedures, including cycles of memoing, coding, data reduction, and theme development [90,91]. Qualitative data will be managed and coded using Dedoose qualitative analysis software (SocioCultural Research Consultants). A team of coders will begin by memoing the data to develop a codebook and then participate in consensus meetings to refine the codebook, resolve coding discrepancies, and ensure consistent code application. Once the data are coded, coders will develop “code summaries” to reduce the data for theme development. Themes will be initially developed by reviewing code summaries, code frequency and repetition, code co-occurrence, and salience of key concepts. TobExA team members from the academic partner organization will lead analysis and engage members from the community partner organization in key analytic processes, including finalizing themes and interpreting results to inform practice and research [91]. To ensure transparency of our qualitative analysis processes, we will maintain an audit trail to document all coding decisions, including modifications to the codebook, and theme development and interpretation procedures.

Quantitative (survey) data will be summarized using descriptive and inferential statistics as appropriate or possible. At a minimum, we will use descriptive statistics to summarize outcomes for co-researchers at each data point (baseline, intermediate, and end line) and examine individual and group changes over time. Individual scales will be scored in accordance with scoring guidelines. Sociodemographic data will be used to characterize the overall sample of co-researchers and advisors to allow for stratified analyses of data as appropriate (eg, comparing engagement experiences for youth collaborators aged <18 y and >18 y).

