#### Navigating Professional Boundaries

Another challenge relates to navigating and maintaining professional boundaries between co-researchers, youth engagement liaisons, and other members of the TobExA team who work with the co-researchers outside of the TobExA study, that is, as service providers at the community partner organization. For example, there have been some occasions in which a co-researcher contacted a specific TobExA team member from the academic partner organization with a request. If the co-researcher was unsatisfied with the response, they would then contact a TobExA team member from the community partner organization with the same request in an attempt to get a different response. Alternatively, a co-researcher would contact one TobExA team member from each of the partner organizations (community and academic) with the same request. If or when responses differed or partners deferred to the other, the co-researcher would become understandably frustrated. This led to duplicative staff efforts (2 individuals attempting to respond to the same request) and the need for lengthy discussion among TobExA team members regarding relatively minor requests.

TobExA team members from the community partner organization have likened this to “staff splitting,” a phenomenon that occurs in health and social services when clients with multiple staff or clinicians responsible for their care engage in actions that create division or polarization among staff in order to influence decisions around their care [95]. While a frequent example of staff splitting in the literature relates to clients seeking more leniency in their treatment plans [96], our experiences have been related to co-researcher expectations regarding responsibilities and processes related to remuneration. Although “staff splitting” has been a new experience to TobExA team members from the academic partner organization, those from the community partner organization (ie, service providers and administrators) have explained that this is a relatively common experience in the provision of social services to youth (and may be aligned with the youth’s developmental stage). They have provided guidance to the TobExA youth engagement liaisons on how to mitigate similar issues in the future.

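### The only field-note prompt on the study aims presupposes that engagement facilitates them, so a theme on that topic may lean favourable

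*Protocol article*

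**What the plan says.** Under Field Notes and Ethnographic Memos, the youth engagement liaisons and other team members who work directly with the youth "will write semistructured field notes after each biweekly meeting with the co-researchers and advisors". Three prompts are listed for these notes:

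1. The first asks for "barriers to and facilitators of equitable and sustainable youth engagement and collaboration".
2. The second asks how the project puts the principles of participatory research into practice.
3. The third asks "how youth engagement and collaboration activities are connected to and facilitating the completion of TobExA study aims".

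The same staff also write weekly unstructured memos. On these the section says: "Memos will document key challenges or needs in the youth engagement process". The exit interviews with co-researchers cover, among other constructs, "team dynamics and communication, key challenges, and opportunities for improvements to youth engagement processes".

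Planned Analysis puts field notes, memos and exit interviews through one thematic analysis. On how themes arise it says: "Themes will be initially developed by reviewing code summaries, code frequency and repetition, code co-occurrence", and it adds the salience of key concepts as a further input. The results are to be used for recommendations to others who engage youth in intervention research.

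**The concern.** The third prompt asks how engagement facilitates the study aims, not whether it does. A writer who follows it will describe help. One who saw delay, wasted effort or no effect has to go outside the question to say so. The writers are also the people who run or support the engagement process, so the record starts from an interested viewpoint and the wording reinforces it.

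The prompt recurs with each note, and repetition of codes counts towards themes. Text of one direction can therefore accumulate on this topic because the template asked for it, and not because the events were of one direction.

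At stake is whether youth engagement advances or burdens the intervention research. The Discussion says that the effectiveness of such strategies has been too little evaluated, and the Conclusions offer this approach as a model for others. A reader of those recommendations would want that question to have been put neutrally.

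**Working it through.** No arithmetic applies. The check sets the passages side by side and asks which question each source puts.

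**Prompts in the field notes**

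| Prompt | Subject | Direction of wording |
|---|---|---|
| 1 | What affects engagement | Both (barriers and facilitators) |
| 2 | How participatory principles are applied | Neutral |
| 3 | What engagement does for the study aims | Favourable only |

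In prompt 1, engagement is the outcome. In prompt 3, engagement is the cause and completion of the aims is the outcome. A writer can answer prompt 1 fully and never say whether engagement slowed the work or used up staff time. Prompt 1 therefore does not balance prompt 3. It does show that the authors had two-sided wording to hand. By count, 1 of 3 prompts is one-directional, and it is the only one on the study aims.

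**Other coded sources**

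- Weekly memos ask for challenges or needs in the engagement process. They are open narrative, so hindrance of the aims may appear, but nothing asks for it.
- Exit interviews cover key challenges and also co-researchers' contributions to the study. They give the co-researchers' view, and co-researchers are less well placed than staff to see costs to staff.
- The focus groups ask what made collaboration challenging, but Planned Analysis does not name their notes among the qualitative data to be analysed.

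All 3 coded sources thus elicit unfavourable content of some kind: field notes through prompt 1, memos, and exit interviews. None is described as asking whether engagement hindered the aims.

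**Route to the results**

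Four inputs to initial theme development are listed: code summaries, code frequency and repetition, co-occurrence, and salience. Frequency is 1 of 4. The wording of prompt 3 can act through it, but only on codes about the contribution of engagement to the aims.

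**Is there anything for the missing question to find?**

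Yes. Navigating Professional Boundaries reports that co-researchers sometimes sent the same request to both partner organizations: "This led to duplicative staff efforts (2 individuals attempting to respond to the same request"). It adds that minor requests took long team discussions. These are costs to the team that prompt 3, as listed, does not request. That they were published also shows that the project as a whole did not miss them.

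**The case against.** The strongest reply is that the evaluation does ask for bad news. Prompt 1 asks for barriers at the same meetings, memos are written weekly and directed at challenges, and exit interviews cover challenges too. The Discussion has five headings of challenges (compensation, boundaries, competing priorities, legitimization, technology) against one section on facilitators. A codebook, consensus meetings, an audit trail and community-partner involvement in finalizing themes are also planned. Nothing says that favourable codes are tallied against unfavourable ones.

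This stands against the stronger reading that a reader might infer: that the field notes as a whole ask only for favourable content, or that the themes in general are tilted. The document does not support either. It does not answer the narrower point, because challenges in running engagement are not the same as effects of engagement on the aims.

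Two further replies have some weight. First, the stated objective is to evaluate engagement by its process and by outcomes among youth collaborators, and not by its effect on the research. That lowers the importance of the point. But prompt 3 itself makes the study aims a topic of the record, and results feed recommendations. Second, the article may paraphrase a template that is not shown, and the words about being connected to the aims are neutral in themselves. If the actual template is already balanced, the point falls. As described in the article, it is not balanced.

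**Conclusion.** The point holds as a minor one, confined to prompt 3 and to any theme on how engagement contributes to the study aims. No listed prompt asks whether engagement hindered, delayed or had no effect on those aims, so such a theme may lean favourable. The document gives no basis for a numerical size, and no actual bias is demonstrated.

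The conclusion assumes that the article gives the prompts substantially as they are used, and that prompt 3 answers are coded together with the other text without being marked.

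**What to change.** For any notes still to be written, put prompt 3 neutrally, for example: *how, if at all, did engagement activities help, hinder or have no effect on completing the study aims?* Check the change against the actual template first.

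For notes already written, flag in the coding any text that answers prompt 3. When a theme on the study aims is developed, do not read the frequency of codes from that text as evidence that engagement helped. Rest the theme on its content and on material from the memos, exit interviews and other prompts.

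The stated study period ends in July 2025 and the article already reports activity up to that month, so few notes may remain to be written and the coding step is probably the more useful half. The rewording is a one-line change. The flag costs some additional coding work, and neither step alters the design or the other analyses.
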